### Statistical analysis

The study includes several necessary methodological resources that will minimize the risk of bias, such as the randomization process, allocation concealment, blinded assessment of the results, and intention-to-treat analysis. A statistician blinded to group allocation will supervise the data entry and analysis. The normality of the variables will be evaluated using the Kolmogorov-Smirnov test and graphs, including histograms and normal distribution plots. For the description of the quantitative variables, the mean and the standard deviation will be used, and for categorical variables, the frequency distribution and percentages. For non-normally-distributed variables, we will use the median, the interquartile range, and the corresponding non-parametric tests. The association between independent categorical variables will be analyzed using the χ2 test or Fisher’s exact test. The means between the two groups will be compared using the one-way analysis of variance (ANOVA). We will analyze the relationship between quantitative variables using correlation coefficients.

We will use logistic regression models to analyze the relationship between fall strategy prevention of 50% reduction in the incidence of falls (yes vs. no) as the dependent variable with the intervention vs. the control group, as the independent variable adjusted for age, gender, total motor MDS-UPDRS, comorbidity severity, and total levodopa equivalent dose. Other pertinent univariate and multivariable analyses will be performed based on the objective type. Also, given the complexity of potential analysis, including a diversity of variables from different origin and measurement properties, advanced statistical methodology (data mining, AI techniques) will be applied as needed. The level of significance will be set at p < 0.05. Statistical analysis will be performed with SPSS V.25.0. (IBM SPSS Statistics for Windows, Armonk, NY, USA).

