### Outcome measures

The study’s primary outcome measure will be the total number of falls in the 4-month (short-term benefit) and 8-month (long-term benefit) after randomization. A fall will be defined as unintentionally coming to rest on the ground or other lower surface without overwhelming external force or a major internal event [56].

Other secondary outcome measures will include: 1) Cost-effectiveness, which will be estimated using natural units of health outcomes, including the incremental cost-effectiveness ratio per fall prevented and cost per extra person avoiding mobility deterioration (identified as an average number of daily steps assessed by wearable sensors); 2) A cost-utility analysis using the EuroQoL will estimate the incremental cost per quality-adjusted life-years (QALY) gain; 3) Short and long-term rate of change from baseline to four and eight months, respectively of motor, NMS, gait, balance, HR-QoL, caregiver burden, and comorbidities severity; 4) Feasibility (completed telemedicine visits) and adherence (dropout rate of telemedicine visits).

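### The blanket normality rule would send costs and fall counts to medians and rank tests, which do not estimate the mean differences that the planned cost-effectiveness ratios need

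*Protocol article*

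**What the plan says.** All references are to the protocol article.

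- **Statistical analysis, the trigger.** "The normality of the variables will be evaluated using the Kolmogorov-Smirnov test and graphs, including histograms and normal distribution plots".
- **Statistical analysis, the consequence.** "For non-normally-distributed variables, we will use the median, the interquartile range, and the corresponding non-parametric tests". Neither sentence exempts any variable.
- **Statistical analysis, the other branch.** "The means between the two groups will be compared using the one-way analysis of variance (ANOVA)". Read with the rule above, this applies to variables judged normal.
- **Outcome measures, primary.** "The study’s primary outcome measure will be the total number of falls in the 4-month (short-term benefit) and 8-month (long-term benefit) after randomization".
- **Outcome measures, economic.** The plan is for cost-effectiveness "including the incremental cost-effectiveness ratio per fall prevented", and for a EuroQoL-based analysis that "will estimate the incremental cost per quality-adjusted life-years (QALY) gain".
- **Specific goals.** Cost-effectiveness against usual care is one of the two first objectives.
- **Statistical analysis, falls model.** The only model named for falls is an adjusted logistic regression on whether a 50% reduction was reached. A further sentence allows other pertinent analyses according to the type of objective.

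**The concern.** An incremental cost-effectiveness ratio is the difference in arithmetic mean cost divided by the difference in arithmetic mean effect. Medians and rank tests supply neither term.

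The rule reaches the variables it suits least. Under In-office assessments, costs include hospitalisation, equipment and adaptation of accommodation, so a long right tail is expected. The Background says that one-third of people with PD fall repeatedly, so fall counts will be skewed too.

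For costs the mismatch has a direction. The programme's cost falls on every treated patient and moves the median up by nearly its full amount. Any saving from fewer hospitalisations sits in a few patients in the tail, which the median hardly registers. A programme that is cost-neutral or cost-saving on the mean can therefore look dearer on the median and in a rank test. The report could then carry a significant rank-test result beside a mean-based ratio that points the other way.

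**Working it through.** **1. The plan's own figure (sample size), to fix the arm size.** Inputs from Sample size: 24% vs 2%, 80% power, 5% error (two-sided assumed).

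n = [1.96·√(2·0.13·0.87) + 0.842·√(0.24·0.76 + 0.02·0.98)]² / 0.22² = (0.932 + 0.378)² / 0.0484 ≈ 35.5, so 36 per group. The plan has 35, at which power is 79.4%. With 9% dropout, 70/0.91 = 76.9; the plan has 76. The figures reproduce within rounding, and 35 per arm is used below. Nothing in this point changes N.

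**2. Costs.** The protocol gives no cost figures, so every input here is an assumption: background cost lognormal with mean EUR 1,500 and log-SD 0.8; a hospitalisation costs EUR 8,000; the programme adds a fixed amount to each treated patient.

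True mean difference = programme cost − 8,000 × (control risk − intervention risk).

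- EUR 600, 10% vs 2.5%: 600 − 8,000 × 0.075 = 0
- EUR 300, 10% vs 6.25%: 300 − 8,000 × 0.0375 = 0
- EUR 200, 10% vs 7.5%: 200 − 8,000 × 0.025 = 0
- EUR 600, 15% vs 5%: 600 − 8,000 × 0.10 = −200

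Simulated results (ranges cover repeated runs):

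| Programme cost (EUR) | True mean difference (EUR) | Average median difference (EUR) | Mann-Whitney: programme dearer |
|---|---|---|---|
| 200 | 0 | about +165 | 10 to 11% |
| 300 | 0 | about +241 | 18 to 19% |
| 600 | 0 | +490 to +506 | 51 to 53% |
| 600 | −200 | +427 to +435 | 36 to 39% |

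When mean costs are equal, a two-sided 5% test of means should call the programme dearer in about 2.5% of trials. A Welch comparison rejected in either direction in about 4 to 6%. In the saving scenario it called the programme dearer in under 2%.

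**3. Does the rule trigger?** In these scenarios the Lilliefors form of the Kolmogorov-Smirnov test rejected normality in 99.7 to 100% of pooled samples. The non-parametric branch would nearly always apply, and histograms would point the same way.

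**4. A second set of assumptions.** Background lognormal with median 1,000 and log-SD 0.6; hospitalisation about 8,000 with spread (mean 8,000 × e^0.08 ≈ 8,666).

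- Programme 400, equal means (10% vs 14.6%): median difference +349; Mann-Whitney calls the programme dearer in 44%; Welch rejects in 4.3%.
- Programme 400, hospitalisation 5% vs 15%: mean difference about −468, median difference +298; Mann-Whitney calls the programme dearer in 33%.
- Programme 800, equal means: Mann-Whitney 88%, Welch 5.2%.

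**5. Falls.** Assumed negative binomial counts, halved by the intervention, 35 per arm:

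| Dispersion k | Means | Mann-Whitney power | Welch power |
|---|---|---|---|
| 0.3 | 6 vs 3 | 19% | 25% |
| 0.5 | 3 vs 1.5 | 30% | 39% |
| 1 | 3 vs 1.5 | 53% | 63% |
| 1 | 6 vs 3 | 60% | 70% |

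The loss is about 5 points at k = 0.3 and about 9 to 10 at k = 0.5 or 1. With identical distributions, Mann-Whitney rejects in 4.7 to 5.1%, so its size is correct. At k = 0.3, means of 6 and 3 both have median 1, so the summary would show a difference of 0 where 3 falls per patient were prevented. At k = 1 the medians are 4 and 2, and the effect is visible.

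**The case against.** **A reader might infer that the ratio itself will be computed from medians and so will be wrong.** The documents do not say so. Outcome measures plans "the incremental cost-effectiveness ratio per fall prevented" separately, and naming that ratio already implies means. The statistical section allows other analyses by objective, and the team includes a health economist. This part of the objection stands: the defect is a general rule that conflicts with the stated estimands, not a wrong ratio already planned.

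**A reader might also infer that a fall reduction vanishes whenever the medians are equal.** Mann-Whitney does not compare medians and can reject when they coincide. At k = 0.3 the comparison of means also misses the halving in most trials. The named logistic responder model does not pass through the normality rule and matches the basis of the sample size. This also stands, so the falls part is limited to a modest loss of power and the lack of a mean or rate effect.

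**The cost percentages rest on assumed inputs.** They do, and a cheaper programme shrinks the effect to about 10%. Nor is a Mann-Whitney rejection at equal means an error about its own hypothesis; it answers a different question from the one the economic objective asks.

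**Bootstrap intervals and a count model are details that an article leaves to a fuller plan.** Their absence alone would be no finding. What remains is that the article states a rule for all variables, and that rule fits these variables badly.

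**Conclusion.** The point holds as a mismatch between a stated rule and the stated estimands. Read as written, skewed costs and total falls go to rank tests, while the economic ratios need differences in arithmetic means.

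For costs, the rank comparison can contradict the mean-based result, including in sign. At equal mean costs the size runs from about 10% to 53% of trials in the main set of assumptions, and from 44% to 88% in the second. These rates depend on the assumed programme cost, hospitalisation cost and hospitalisation risks. The mechanism itself needs only a cost borne by all treated patients and savings confined to a few.

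For falls the harm is smaller: no mean or rate effect for the primary count, and about 5 to 10 points of power under the assumed counts. The sample size is unaffected. The documents do not support the claim that the planned ratio will be wrong. The change is worth making because it is cheap and removes the risk of two conflicting cost results.

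**What to change.** - Exempt costs, QALYs and fall counts from the normality rule.
- Compare costs and QALYs on arithmetic mean differences with bootstrap intervals, whatever the shape of the distribution, and build both ratios from those differences.
- Analyse total falls with a negative binomial rate model, reporting the rate ratio and the mean number of falls prevented. The latter then serves as the denominator of the ratio per fall prevented.
- Keep medians and interquartile ranges for these variables as description only.

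The cost is a few sentences of wording, a bootstrap routine and one count model: minor extra analysis work, with no new data and no change to the number of patients.

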## Procedure

After signing the informed consent form, investigators will invite PD patients to participate in this randomized controlled trial. Patients will be randomly assigned using a block gender-randomization Excel calculator [male/female: intervention/control groups), providing an equal number of males and females with PD in the control/intervention groups (1:1). There will be no personal expenses for the participant during the study; instead, all assessments will be free, including the neurologist, nurse, psychologist, and occupational therapist evaluations. The patients will be contacted by phone to confirm they attended the treatment sessions. Likewise, reports of the assessments performed during the study will be available to improve patient adherence to the intervention protocols.

Two study phases will be established (Fig 1). In the *first phase* (baseline-4^th^ month), short-term benefits will be assessed. All participants will be evaluated at baseline and four months in office. Patients allocated in the intervention group will be receiving the telemedicine fall prevention program. The occupational therapist will bring the equipment for videoconferencing to the patients’ home, set up the room for physical therapy, and evaluate the patient’s risk of performing different exercises according to the patient’s capabilities and home environment. In the *second phase* (5^th^-8^th^month), long-term benefits will be assessed. All patients allocated in the intervention group will discontinue the telemedicine program at the end of the 4^th^ month. All patients will receive standard medical care provided by the movement disorder neurologist and nurse, with a final visit at eight months from baseline.

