## Statistical analysis

### Sample size

We calculated the sample size using the Epidat^®^ 4.1 statistical software. Considering that a 50% fall reduction in the number of falls compared to baseline will be obtained in 24% of the participants in the intervention group and 2% in the control group, we estimated that 70 patients (35 per group) would provide 80% power (5% probability of type 1 error) with a confidence level of 95%. By assuming a 9% dropout rate, a total sample of 76 patients will be then included in this study.

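### The only method named for comparing continuous scores between arms, one-way ANOVA, uses neither the baseline score nor the gender randomisation factor as a covariate, so the secondary change-score comparisons are less precise than they could be

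*Protocol article*

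**What the plan says.** The Outcome measures section defines the third secondary outcome as "Short and long-term rate of change from baseline to four and eight months, respectively of motor, NMS, gait, balance, HR-QoL, caregiver burden, and comorbidities severity". Table 1 schedules almost every scale at baseline, month 4 and month 8; the two satisfaction instruments are exceptions, at month 8 only.

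The Statistical analysis section gives the group comparison for continuous variables in one sentence: "The means between the two groups will be compared using the one-way analysis of variance (ANOVA". The alternative is "For non-normally-distributed variables, we will use the median, the interquartile range, and the corresponding non-parametric tests", with normality judged by the Kolmogorov-Smirnov test together with graphs.

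The Procedure section describes a gender-restricted randomisation: "Patients will be randomly assigned using a block gender-randomization Excel calculator". Covariates are named in one place, the logistic model for a 50% fall reduction, which is "adjusted for age, gender, total motor MDS-UPDRS, comorbidity severity, and total levodopa equivalent dose". The same paragraph adds an open statement: "Other pertinent univariate and multivariable analyses will be performed based on the objective type".

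**The concern.** A one-way ANOVA has group as its only factor. Applied to a change score, it subtracts the baseline with a fixed coefficient of 1 instead of estimating how strongly baseline predicts follow-up. Two things follow. The variance of the treatment difference is larger than it need be. Also, if the arms happen to differ at baseline, part of that difference carries into the estimated change through regression to the mean. With 38 patients per arm such differences are to be expected.

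Gender restricts the randomisation but does not enter this comparison. Where gender predicts a score, leaving it out makes the interval wider than the design warrants. The non-parametric alternative is not stated to be adjusted either, and because it is chosen from the data, the effect measure for a scale could differ between months 4 and 8.

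At stake is the precision of the motor, non-motor, gait, balance, quality-of-life and caregiver-burden results. The trial was not sized for any of these.

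**Working it through.** **The plan's own figure.** The only sample-size calculation concerns a binary responder: a halving of falls that "will be obtained in 24% of the participants in the intervention group and 2% in the control group". With pooled variance, two-sided 5%, 80% power and no continuity correction:

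- mean proportion = (0.24 + 0.02)/2 = 0.13
- n per arm = [1.96 × √(2 × 0.13 × 0.87) + 0.8416 × √(0.24 × 0.76 + 0.02 × 0.98)]² / 0.22² = 1.310² / 0.0484 = 35.5, so 36

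The plan states 35 per arm, at which power is 79.4%. The figure reproduces, but it says nothing about the scales. It supplies only the n of 35 per arm used below.

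**Variance of the treatment difference.** Take equal SDs at baseline and follow-up (set to 1) and a baseline to follow-up correlation r. The document gives no r, so 0.3 to 0.9 is an assumed range. Per-patient variance:

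- one-way ANOVA on change: 2(1 − r)
- ANCOVA with baseline as covariate: 1 − r²
- ratio: (1 − r²) / [2(1 − r)] = (1 + r)/2

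The N column is 70 × ratio. The power column is Φ(2.80/√ratio − 1.96), for an effect that change-score ANOVA would detect with 80% power.

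| r | Change score | ANCOVA | Ratio | ANCOVA N matching 70 | Power under ANCOVA |
|---|---|---|---|---|---|
| 0.3 | 1.40 | 0.91 | 0.65 | 45.5 | 93.5% |
| 0.5 | 1.00 | 0.75 | 0.75 | 52.5 | 89.9% |
| 0.7 | 0.60 | 0.51 | 0.85 | 59.5 | 86.0% |
| 0.9 | 0.20 | 0.19 | 0.95 | 66.5 | 82.0% |

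Confidence-interval width scales with √ratio: 0.81, 0.87, 0.92 and 0.97.

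**Fixed effect.** For a true difference of 0.5 SD with 35 per arm, power under change-score ANOVA against ANCOVA is:

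- r = 0.3: 42% against 59%
- r = 0.5: 55% against 68%
- r = 0.7: 77% against 83%
- r = 0.8: 91% against 94%

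**Chance imbalance.** The standard error of a baseline mean difference is √(2/35) = 0.24 SD. An imbalance of one standard error moves the change-score estimate by (1 − r) × 0.24: 0.17, 0.12, 0.07 and 0.02 SD at r = 0.3, 0.5, 0.7 and 0.9. ANCOVA removes this shift.

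**If the ANOVA were run on raw follow-up scores.** The ratio becomes 1 − r², that is 0.91, 0.75 and 0.51 at r = 0.3, 0.5 and 0.7. An 80% power would become 83.6%, 89.9% and 97.5%. The advantage of adjustment then grows with r.

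**Gender.** The gain depends on how strongly gender predicts each score. The document gives nothing on this, so no figure can be computed.

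**The case against.** The ANOVA sentence is generic. It sits in a list with normality checks, descriptive statistics and correlations, names no outcome or visit, and would fit a baseline comparison of the arms equally well. The plan also announces further multivariable analyses, and a condensed article may leave covariates to a fuller document. Part of this stands: the link to the change scores is an inference from the Outcome measures section. But one-way ANOVA is the only parametric comparison of means that is named, and the open statement identifies no outcome, model or covariate. It allows adjustment without committing to it.

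Stronger readings are tempting, and the document does not support them:

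- A reader might infer that baseline is ignored altogether. If change scores are analysed, baseline is subtracted; what is missing is its use as a covariate.
- A reader might infer bias. Under randomisation the unadjusted comparison is unbiased, and regression to the mean acts in both arms. A chance imbalance affects the particular estimate, not its expectation.
- A reader might infer that gender is left out of the plan. It is a covariate in the logistic fall model.
- A reader might infer that patients are recruited needlessly. The sample size rests on the binary fall responder, so the N column above only expresses lost precision.
- A reader might conclude that every scale needs a linear model. That would suit coarse ordinal measures poorly. Hoehn & Yahr, for example, is restricted at entry to stages below 3.
- A reader might take the switch to rank tests as driven by a test alone. The plan also uses graphs.

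**Conclusion.** The point holds as a matter of efficiency and of consistency with the randomisation, confined to secondary continuous outcomes. Replacing change-score ANOVA by baseline-adjusted ANCOVA would cut the variance of the treatment difference by (1 − r)/2: 35%, 25%, 15% and 5% at r = 0.3, 0.5, 0.7 and 0.9. The gain is therefore substantial for scales that track weakly over time and slight for those that track closely.

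This rests on equal variances at baseline and follow-up, on an assumed r, and on reading the ANOVA sentence as applying to the change scores. The further gain from gender is of unknown size. Type I error is not inflated, and the primary fall analysis is unaffected.

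**What to change.** For the continuous multi-item scales with a baseline measurement, replace one-way ANOVA in the Statistical analysis section with either ANCOVA at each visit (group, baseline score, gender) or one mixed model per scale (group, visit, group-by-visit, baseline score, gender). Report adjusted differences with 95% confidence intervals at months 4 and 8.

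State the method for each scale in advance instead of choosing it by normality testing. Keep an ordinal or rank-based analysis for coarse ordinal measures such as Hoehn & Yahr, the malnutrition screening tool, the Frail Scale and the Fried index.

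The cost is a change of wording and the work of assigning each scale to a method. The baseline scores and gender are already collected, and the named software fits these models.

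### The logistic model planned for the fall-reduction responder has about nine expected responders for six effects; in about half of trials its ordinary odds ratio and Wald test would be unusable.

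*Protocol article*

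**What the plan says.** The sample-size section of the protocol article defines a responder as a patient with a 50% reduction in falls from baseline. It assumes response in "24% of the participants in the intervention group and 2% in the control group" and states that 35 patients per group "would provide 80% power (5% probability of type 1 error) with a confidence level of 95" percent. On dropout it says: "By assuming a 9% dropout rate, a total sample of 76 patients will be then included in this study". That makes 38 per arm at entry.

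The statistical analysis section takes the same yes/no responder as the dependent variable of a logistic regression, with group "as the independent variable adjusted for age, gender, total motor MDS-UPDRS, comorbidity severity, and total levodopa equivalent dose". Counting group, the model has six effects besides the intercept. It is the only model the article names for the endpoint on which the trial was sized.

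The article does not say whether the group coefficient is judged by a Wald, likelihood-ratio or penalised test. The χ2 test and Fisher's exact test are listed for categorical variables in general. The section on outcome measures makes the total number of falls the primary outcome.

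**The concern.** A logistic model estimates log odds. If one arm has no responders, the maximum-likelihood log odds ratio for group has no finite value, and its standard error grows without bound. The Wald statistic then falls towards zero however strong the evidence, and the Wald interval says nothing. With a planned control rate of 2% in 35 patients, this is close to an even chance.

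The analysis would therefore fail where the data most favour the intervention. For example, 6 of 35 responders against 0 of 35 gives a two-sided Fisher p-value of 2 × C(35,6)/C(70,6) = 2 × 1,623,160/131,115,985 = 0.025. The ordinary logistic fit to the same table gives no finite odds ratio and no usable Wald test.

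A separate strain is that nine or so events must also support five adjustment terms. The sample-size calculation did not allow for this, since it compares two unadjusted proportions.

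**Working it through.** **Inputs.** From the sample-size section: 24% and 2% responders, 35 per arm evaluable, 76 enrolled (38 per arm), 5% error and 80% power. From the statistical analysis section: group plus five covariates. Two-sided testing is assumed, because it reproduces the stated size.

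**1. The plan's own figure.** The pooled two-proportion formula without continuity correction, with mean rate 0.13, gives

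n = [1.96 × √(2 × 0.13 × 0.87) + 0.8416 × √(0.24 × 0.76 + 0.02 × 0.98)]² / 0.22² = (0.932 + 0.378)² / 0.0484 ≈ 35.5 per arm.

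By the same formula, power at 35 per arm is 79.4%. The stated 35 per group and 80% are therefore reproduced, for an unadjusted large-sample comparison.

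**2. Expected responders.**
- 35 per arm: 35 × 0.24 + 35 × 0.02 = 8.4 + 0.7 = 9.1, or 9.1/6 ≈ 1.5 per effect.
- 38 per arm: 9.12 + 0.76 = 9.88, or about 1.6 per effect.

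**3. Chance of no control responder.** 0.98^35 = 49.3%; 0.98^38 = 46.4%.

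**4. Unadjusted tests, exact binomial enumeration at 24% vs 2%.**

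| Test | 35 per arm | 38 per arm |
|---|---|---|
| Pearson χ2, uncorrected | 87.9% | 90.5% |
| Likelihood ratio | 88.6% | 90.9% |
| Fisher's exact | 71.7% | 77.8% |
| Wald, infinite odds ratio counted as non-significant | 28.8% | 35.5% |

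**5. The planned six-effect model, simulated at 35 per arm.** There were 1,500 trials per scenario (Monte Carlo standard error about 1.2 points or less). Sex was balanced by arm, and the four other covariates were independent standard normal variables. The first figure in each cell is for non-prognostic covariates. The second is for a log odds ratio of 0.5 per SD for each continuous covariate.

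| Quantity | 24% vs 2% | 13% vs 13% (type I error) |
|---|---|---|
| Fits that separated | 49.6%, 50.2% | 3.0%, 3.2% |
| Wald, separated fits non-significant | 32.5%, 34.0% | 2.5%, 3.3% |
| Ordinary likelihood ratio | 87.7%, 89.9% | 6.9%, 8.1% |
| Firth penalised likelihood ratio | 81.1%, 81.9% | 3.5%, 4.3% |

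Repeat simulations put Wald power at 31–34% and Firth power at 80–82% at 35 per arm. At 38 per arm they gave a non-finite group effect in 47–48% of trials and Wald power of 36–37%.

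**6. Dependence on the control rate.** The article gives no range for the 2%. If the rate were 5%, 10% or 20% (assumed values), the chance of no control responder at 35 per arm would be 0.95^35 = 17%, 0.90^35 = 2.5% or 0.80^35 = 0.04%.

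**The case against.** **Power.** A reader might infer that the trial cannot deliver its 80% power. The document does not support that. It names no test for the group coefficient, and an infinite estimate is not the same as lost power. Power falls to about one third only under the Wald test. The same six effects in the same patients give about 80–82% power under Firth, with type I error below 5%.

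**Cause.** A reader might also blame the covariates for the infinite odds ratio. It comes mainly from the 2% control rate. With no control responder the estimate is infinite even without covariates, and unadjusted Wald power (28.8%) is no better than adjusted. Cutting covariates eases the events-per-effect problem but does not cure separation.

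**Fisher's test.** The article lists χ2 or Fisher without a rule for choosing, so 72% is not the plan's power. It is the power if Fisher is the test chosen.

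**Status of the model.** The article does not call the logistic model primary; its primary outcome is the number of falls. Whether a count model should carry the main comparison is a different question, which this point does not settle.

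**Detail left to an analysis plan.** The choice of test and the handling of separation often sit in an unseen document, and their absence here is not the complaint. The article does fix the model and its covariate list, and that stated choice conflicts with its own planning rates.

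**Control rate.** If more control patients respond, separation becomes rare. That is true, but the analysis should work under the rates used to size the trial.

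**Conclusion.** The point holds in this limited form. Under the protocol's own rates, the stated model has about 1.5 expected responders per effect. Fitted by ordinary maximum likelihood, it gives a non-finite odds ratio and an unusable Wald test and interval in about half of trials. Neither ordinary test of the group effect meets both design targets: Wald has about 31–34% power, and the likelihood-ratio test has about 88–90% power with about 7–8% type I error. A penalised test does meet them, so the fault lies in the stated method and covariate list, not in the sample size.

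The event counts and the 49% and 46% follow directly from the documents. The power and error figures for the adjusted model rest on two-sided 5% testing, independent covariates with the effects described above, separated fits counted as non-significant for Wald, and a common rate of 13% for type I error.

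**What to change.** Before unblinding, amend the statistical analysis section as follows.

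1. Fit the responder model by Firth-penalised logistic regression, with penalised likelihood-ratio tests and profile penalised-likelihood intervals. Exact logistic regression is an alternative if the remaining covariates are few and categorical.
2. Cut the covariates to the few that about nine events can support. An example is gender, which is the randomisation factor ("providing an equal number of males and females with PD in the control/intervention groups (1:1"), and one prespecified prognostic baseline variable.
3. State power for the test that will be used. For Firth this is about 80–82% at 35 per arm, simulated with all six effects; rerun it for the reduced model. If an unadjusted Fisher's exact test is chosen instead, state 72% at 35 per arm and 78% at 38.
4. Check that the named software, SPSS V.25.0, offers the chosen method, and name another package if it does not.

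The cost is protocol or analysis-plan wording and slightly more analysis work. No extra patients are needed. With Firth the stated 80% power can stand; only a choice of Fisher would lower it.
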